## Abstract

**OBJECTIVES::**

Management of hypotension is a fundamental part of pediatric critical care, with cardiovascular support in the form of fluids or vasoactive drugs offered to every hypotensive child. However, optimal blood pressure (BP) targets are unknown. The PRotocolised Evaluation of PermiSSive BP Targets Versus Usual CaRE (PRESSURE) trial aims to evaluate the clinical and cost-effectiveness of a permissive mean arterial pressure (MAP) target of greater than a fifth centile for age compared with usual care.

**DESIGN::**

Pragmatic, open, multicenter, parallel-group randomized control trial (RCT) with integrated economic evaluation.

**SETTING::**

Eighteen PICUs across the United Kingdom.

**PATIENTS::**

Infants and children older than 37 weeks corrected gestational age to 16 years accepted to a participating PICU, on mechanical ventilation and receiving vasoactive drugs for hypotension.

**INTERVENTIONS::**

Adjustment of hemodynamic support to achieve a permissive MAP target greater than fifth centile for age during invasive mechanical ventilation.

**MEASUREMENTS AND MAIN RESULTS::**

Randomization is 1:1 to a permissive MAP target or usual care, stratified by site and age group. Due to the emergency nature of the treatment, approaching patients for written informed consent will be deferred until after randomization. The primary clinical outcome is a composite of death and days of ventilatory support at 30 days. Baseline demographics and clinical status will be recorded as well as daily measures of BP and organ support, and discharge outcomes. This RCT received Health Research Authority approval (reference 289545), and a favorable ethical opinion from the East of England—Cambridge South Research Ethics Committee on May 10, 2021 (reference number 21/EE/0084). The trial is registered and has an International Standard RCT Number (reference 20609635).

**CONCLUSIONS::**

Trial findings will be disseminated in U.K. national and international conferences and in peer-reviewed journals.

RESEARCH IN CONTEXTThere is no high-quality evidence from randomized clinical trials comparing mean arterial pressure (MAP) targets in critically ill children.Emerging evidence from trials supports the use of permissive MAP targets in critically ill adults.The Protocolised Evaluation of Permissive Blood Pressure Targets Versus Usual Care trial will test the hypothesis that the benefits associated with a permissive MAP target will outweigh the risks in hypotensive critically ill children.

Hypotension is common in critically ill children and can compromise tissue perfusion and organ function. It is associated with increased risk of multiple organ failure and death after cardiac arrest and sepsis (1, 2). Hypotension is also associated with poor neurologic outcomes, particularly after cardiac arrest (1). In a review of 2005–2011 pediatric emergency practice in London, United Kingdom, the presence of septic shock at the time of critical care transport was associated with mortality of 20% (3).

Mean arterial pressure (MAP), reflecting perfusion pressure, is usually targeted in PICUs. Interventions to increase MAP may include IV fluids and vasoactive drugs. In the 2018 U.K. Paediatric Intensive Care Audit Network (PICANet, www.picanet.org.uk) dataset, around 30% of the 20,000 children admitted to U.K. PICUs received vasoactive drugs during their critical illness (4). Observational data from two London PICUs, obtained between 2009 and 2016, to look at usual practice (5), demonstrated that observed blood pressure (BP) was higher than 50th centile for age. However, though treating hypotension is beneficial, there are potential harms associated with the interventions. A systematic review of the literature from March 2017 showed an association between excessive IV fluids and prolonged PICU stay and increased mortality (6). Most vasoactive drugs cause vasoconstriction, which may reduce blood flow and impair end-organ function. Central venous catheters, sited to administer vasoactive drugs, are associated with thrombosis and infection, particularly in small children. The benefit-versus-harm balance when treating hypotension is complex, the threshold for harm is not clear, and a lower MAP than normal may be adequate. Aiming at a lower MAP than normal is referred to as “permissive hypotension.” Such a strategy echoes other permissive treatment strategies currently being evaluated in pediatric intensive care (7). The aim of the Protocolised Evaluation of Permissive BP Targets Versus Usual Care (PRESSURE) trial is to provide high-quality evidence to inform MAP targets in critically ill children.

In 2021, there was no high-quality evidence from randomized clinical trials (RCTs) comparing MAP targets in critically ill children. The 2020 Surviving Sepsis Campaign International Guidelines for the Management of Septic Shock and Sepsis-Associated Organ Dysfunction in Children suggested using a 5th–50th centile MAP target, while also noting the lack of RCT data in this area and highlighting the need for clinical trials (8). Advanced pediatric life support guidelines recommend targeting systolic BP at 5 mm Hg higher than the 50th centile without any trial-based evidence to support this practice. In the 1991–2018 pediatric literature, the study of BP targets in sepsis was, in general, part of retrospective examinations about bundles of care (9–14). In the adult patient literature about permissive hypotension, two separate RCTs were conducted during 2010–2011 (15) and 2013–2014 (16); when pooled, meta-analyses were carried out together in 2017 (17), suggesting that targeting higher MAP values of between 75 and 85 mm Hg may be associated with an increased risk of death in some older critically ill patients. The most recent RCT in adults recruited 2600 critically ill older patients with vasodilatory hypotension, in 2017–2019 (18), the “65 Trial,” showed no harm from a lower MAP target. There are no similar trial data in children. The PRESSURE trial will test the hypothesis that the benefits associated with a permissive MAP target in hypotensive critically ill children will outweigh the risks, improving outcomes and decreasing costs.

## MATERIALS AND METHODS

### Primary Objective

The primary objective is to estimate the clinical and cost-effectiveness of permissive MAP target (i.e., lower MAP target fifth centile for age) on a composite outcome of mortality and duration of invasive mechanical ventilation (IMV) at 30 days (i.e., rank-based analysis with death ranked as worse than 30 d of IMV), when compared with usual care.

### Design and Setting

PRESSURE is a pragmatic (19), multicenter, parallel-group RCT with integrated economic evaluation in infants and children accepted for admission to any of 18 National Health Service (NHS) PICUs across the United Kingdom and their regional retrieval services. It has previously been mentioned in the 2022 Paediatric Critical Care Society Study Group (PCCS-SG) summary of studies, published in *Pediatric Critical Care Medicine* (7).

### Screening and Randomization

Potentially eligible patients admitted (or accepted for admission) to participating PICU will be screened against the inclusion/exclusion criteria by the local clinical or transport team (**Table 1**). Patients will be randomized in a ratio 1:1 to either usual care or a permissive MAP target (fifth centile for age), stratified by site and age group (< 1, 1–3, ≥ 3 yr), to ensure balanced strata sizes. Randomization must occur within 6 hours of all the eligibility criteria being satisfied (Table 1). Randomization will be done by an automated randomization server accessible both by telephone and via web browser. The randomization sequence is computer-generated and will use variable block sizes to strengthen allocation concealment.

**TABLE 1. T1:** Eligibility Criteria

Inclusion criteria
• Age > 37 wk corrected gestational age and < 16 yr
• Enrolled within 6 hr of first meeting all the following criteria;
◦ Accepted for or admitted to a participating PICU
◦ Face-to-face contact with PICU staff or transport team
◦ On invasive mechanical ventilation
◦ Receiving a continuous infusion of vasoactive drug for hypotension
◦ Vasoactive drug expected to continue for at least 6 hours or more^a^
Exclusion criteria
• Admitted postcardiac surgery
• Known cardiomyopathy^b^
• Neonates with suspected or proven duct-dependent circulation
• Acute brain injury^c^
• Currently being treated for pulmonary hypertension
• Admitted with malignant hypertension
• Death perceived as imminent
• Previously recruited to Protocolised Evaluation of Permissive Blood Pressure Targets Versus Usual Care trial

a “Vasoactive drug expected to continue for at least 6 hours or more” is at the discretion of the clinical team.

b “Known cardiomyopathy” refers to conditions known at time of randomization.

c “Acute brain injury” refers to traumatic brain injury or any acute or evolving neurologic condition requiring a neurointensive care strategy. In general, patients post cardiac arrest would not be eligible for randomization due to the high likelihood of acute brain injury. If the clinical team can rule out this contraindication (e.g., brief in-hospital cardiac arrest, when acute brain injury is not suspected) the patient would be eligible.

### Intervention and Concomitant Care

Following randomization, the allocated treatment will be commenced as soon as practically possible. In the intervention group, this means adjustment of vasoactive drugs and other therapies to achieve a MAP within the permissive MAP target band (lower MAP target fifth centile for age [20], see **Table 2**; and **Supplemental materials**, http://links.lww.com/PCC/C509 for details). In the usual care group, the MAP target is determined by the clinical team. The choice of treatments to achieve the MAP target and all other care is at the discretion of the clinical team.

**TABLE 2. T2:** Protocolised Evaluation of Permissive Blood Pressure Targets Versus Usual Care Permissive Mean Arterial Pressure Target Bandings

Age Range (Completed Months/Yr)	Target Range (mm Hg)
37 wk–6 mo	40–43
> 6 mo–< 1 yr	40–45
≥ 1–3 yr	45–50
4–9 yr	50–55
≥ 10 yr	55–60

### Consent Procedures

Consent will be sought for the child (patient) from a parent/legal guardian with parental responsibility. Children become eligible for PRESSURE during a period of critical illness. Consequently, PRESSURE uses a “research without prior consent” model. Once a patient is screened and confirmed as eligible for the study, they will be randomized and the randomly assigned treatment will be commenced as soon as practically possible. This model, developed in line with the Consent Methods in Paediatric Emergency and Urgent Care Trials study guidance (21) has been found to be acceptable to parents/guardians, as well as to clinicians, in several PCCS-SG RCTs (22–26).

Once notified of the randomization of a patient into the study, a trained, delegated member of the site research team will approach parents/legal guardians of the patient as soon as possible to discuss the study, usually within 24–48 hours. A patient information sheet and consent form will be provided indicating: 1) the information has been read and understood, 2) consent is given for continuation in the trial, access to medical records, and linkage with routinely collected national data (e.g., national death registration data via NHS Digital or equivalent), 3) receipt of follow-up questionnaires, and 4) anonymized data to be shared in future.

A modification of the consent procedure will be used in two situations when either the patient: 1) is discharged from hospital before obtaining consent or 2) dies before consent is sought. In the former, the local research team will contact the parent/guardian, initially by telephone and then by post, for consent. If there is no response after 4 weeks, postal contact will be made again. If no consent form is received within 4 weeks of the second letter, the parent/guardian will be advised that the participant will be included in the trial unless they notify the research team otherwise. In the second situation, the local research team will establish the most appropriate clinical/research team member and time to notify the parents/guardians of involvement in the trial. If approach for consent before their departure from hospital is not deemed appropriate, then the same process as in the first situation, with contact by post, will be followed.

### Safety Monitoring

Adverse event (AE) reporting will follow the Health Research Authority guidelines on safety reporting in studies that do not involve investigational medicinal products (27). The following events have been prespecified as potential AEs that could be related to trial MAP target (or associated interventions): myocardial ischemia, arrhythmia, digital or limb ischemia, central line-associated bloodstream infection, thrombus related to central line insertion, skin necrosis related to administration of vasoactive via peripheral line, severe acute renal failure (as defined by the Kidney Disease Improving Global Outcomes criteria for stage 3), acute cerebral ischemia or infarction. These are reported if observed in participants from the time of randomization, for the duration of the treatment period, defined as the time the patient is in PICU during the acute hospital admission. This includes readmission to PICU from another inpatient care area (if the date of readmission is within 30 d from randomization).

Occurrences of specified, expected AEs will be recorded for all randomized patients. Considering that all infants and children eligible for PRESSURE are critically ill and at increased risk of experiencing AEs due to the complexity of their condition, occurrences of nonspecified AEs will only be reported if they are serious and are considered to be related to lower MAP values and/or higher doses of vasoactive agents required to maintain higher MAP values (i.e., “possibly,” “probably,” or “definitely”). Any event meeting these criteria will be considered a serious adverse event (SAE) and must be reported to the Intensive Care National Audit and Research Centre (ICNARC) Clinical Trials Unit (CTU). If the SAE is evaluated as a related and unexpected SAE, the ICNARC CTU will report to the research ethics committee (REC) within 15 calendar days.

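### The causal test for reporting unlisted serious adverse events omits IV fluids and other therapies used to reach the MAP target, and is narrower than the scope the same section sets for its listed events

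*Protocol article*

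**What the plan says.** The Safety Monitoring section of the protocol article sets out two routes by which an adverse event is counted.

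- **Listed events.** A fixed list is introduced as "potential AEs that could be related to trial MAP target (or associated interventions". It covers cardiac, limb and cerebral ischemic events, arrhythmia, central-line infection and thrombus, skin necrosis from peripheral vasoactive infusion, and "severe acute renal failure (as defined by the Kidney Disease Improving Global Outcomes criteria for stage 3". On recording, the rule is: "Occurrences of specified, expected AEs will be recorded for all randomized patients".
- **Unlisted events.** Here "occurrences of nonspecified AEs will only be reported if they are serious" and are also "considered to be related to lower MAP values and/or higher doses of vasoactive agents required to maintain higher MAP values", with relatedness graded as possible, probable or definite. Events that pass become SAEs and go to the trials unit. Those judged related and unexpected go on to the ethics committee within 15 calendar days.

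Two other places bear on the scope of the second route. The introduction states: "Interventions to increase MAP may include IV fluids and vasoactive drugs". It then gives a harm for the first of these: "A systematic review of the literature from March 2017 showed an association between excessive IV fluids and prolonged PICU stay and increased mortality". The Intervention and Concomitant Care section describes the intervention as "adjustment of vasoactive drugs and other therapies to achieve a MAP within the permissive MAP target band" and leaves the choice of treatments to the clinical team.

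**The concern.** The trial compares two pressure targets, and the target works through whatever is given, reduced or withheld to reach it. The article itself names two such treatments, fluids and vasoactive drugs. The test for unlisted events admits lower pressure as a cause on one side and higher vasoactive dosing on the other. It therefore covers only one of the two treatments named for raising pressure. Because the rule says events are reported only if they meet the test, this is a closed rule and not an incomplete set of examples.

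What is at stake is event-level safety reporting. SAE status, notification of the trials unit and the 15-day ethics report all depend on passing this test. A serious event that a site believes was caused by fluid given to reach the target has no route into that chain unless it happens to be on the list. This matters more than usual because children are randomized before consent is sought, and because attribution is made by staff who know the allocation, so the criteria need to be clear and the same for both arms.

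**Working it through.** No arithmetic applies. The claim concerns the wording of a rule and depends on no rate, sample size or alpha. The check sets the relevant statements side by side and then traces types of event through the rule.

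**Step 1. Scope of causes in each place**

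| Place in the protocol article | Causes or treatments covered | IV fluids included? |
|---|---|---|
| Introduction, means of raising MAP | IV fluids, vasoactive drugs | Yes, by name |
| Introduction, harms of treatment | Excess fluid; vasoconstriction from vasoactive drugs; complications of the lines sited to give them | Yes, by name |
| Intervention and Concomitant Care | Vasoactive drugs and other therapies | Yes, under other therapies |
| Safety Monitoring, scope of the listed events | Trial MAP target or associated interventions | Yes, under associated interventions |
| Safety Monitoring, test for unlisted events | Lower MAP; higher vasoactive doses needed for higher MAP | No |

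The last row is narrower than the other four, and the row above it is from the same section.

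**Step 2. Does the list close the gap?** No listed event is specific to fluid. Stage 3 renal failure could arise partly through fluid, but the list contains nothing such as fluid overload or pulmonary edema. So the list catches some consequences of fluid, not all.

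**Step 3. Trace events through the rule**

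1. *A listed event, such as stage 3 renal failure, that the site blames on fluid.* Recorded, because listed events carry no attribution test.
2. *A serious unlisted event in a child receiving both fluid and vasoactive drug, judged at least possibly related to lower MAP or to higher vasoactive dosing.* Reported, because a grade of possible is enough.
3. *A serious unlisted event that the site attributes to fluid alone.* Not reported as an SAE. It fails the test, does not go to the trials unit by this route, and so cannot trigger the 15-day report even if unexpected. This holds in both arms.
4. *Death, longer ventilation, longer PICU stay or renal replacement in which fluid played a part.* Counted as an outcome and compared by arm whatever the cause (Outcome Measures, Table 3).

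**Result.** The defect is real and is limited to the third type.

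**The case against.** The strongest reply is that little is lost. The two consequences that the introduction links to excess fluid, mortality and prolonged PICU stay, are both trial outcomes. Mortality is also in the primary composite with ventilation duration, and renal replacement is a secondary outcome. Listed events are recorded regardless of attribution. Every child is on a vasoactive infusion at entry (Table 1), so many serious events could be judged at least possibly related to vasoactive dosing. The section gives a reason for restricting reports, namely that these children are at high risk of adverse events anyway. The article also condenses a full protocol, and the case report forms, which are not shown, may define relatedness more widely.

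Most of this stands, and it rules out three stronger readings that a reader might infer.

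- *That fluid harm goes uncounted in the trial.* The outcomes and listed events above contradict this.
- *That the monitoring committee would see nothing of it.* The Oversight section gives the committee a safety remit that is not confined to SAE reports. An interim analysis is planned after 30-day follow-up of 50% of patients, with stopping possible for harm. Table 4 collects cointervention and safety data during the stay.
- *That the SAE comparison is tilted in a known direction.* The article gives no fluid use by arm. Missed events would fall mainly in usual care if that arm received more fluid, and mainly in the permissive arm if teams there replaced vasoactive drug with fluid. Neither can be established.

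The reply does not remove the inconsistency. Arm-level outcomes show that one group did worse. They do not identify the therapy responsible in a particular child, and they prompt no review of an individual event. A reason for limiting reports to serious, related events is not a reason for leaving out one of the related causes. If the full protocol is wider, the article misstates the rule and should be corrected.

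**Conclusion.** The point holds as a wording defect in a stated rule. The test for unlisted serious events is narrower than the scope of the section's own list, than the rationale and than the description of the intervention. Its effect is that a serious unlisted event attributed to fluid alone is not reported as an SAE and does not reach expedited review, in either arm.

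The size is minor to moderate. The number of such events cannot be estimated, because the documents give neither a rate nor fluid volumes. Sample size, power, the primary analysis and the outcome comparisons are unaffected.

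The conclusion assumes that sites apply the rule literally and that the full protocol and case report forms, which were not available, use the same test. It is still worth correcting, because it concerns the safety of individual children enrolled before consent and the correction is simple.

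**What to change.** Replace the causal test for unlisted serious events with: *related to the trial MAP target or to any intervention used to achieve it, including IV fluids*. Apply it identically in both arms, and keep the existing seriousness requirement and grades of relatedness. This brings the test into line with the scope the section already uses for its listed events. Check that the full protocol and the event form carry the same wording.

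The cost is a wording change to the safety section and, if it repeats the test, to the event form, with slightly more events for sites to report and the trials unit to process. No treatment, outcome or analysis changes. Adding a fluid-specific event to the prespecified list is not needed for this correction. That would be a separate design judgement, requiring a definition and assessment in every child.

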## OUTCOME MEASURES

The primary clinical effectiveness outcome is a composite of mortality and duration of IMV, defined by the U.K. Paediatric Critical Care Minimum Dataset (28), from randomization to day 30. This will include any periods of reintubation. This outcome measure was chosen based on previous qualitative work which highlighted the child “looking and feeling more like themselves” and “time on machines” as the most important outcomes for parents (29). As intensive care interventions for cardiovascular support will be different between the intervention and control arms, the focus of the primary outcome measure is on respiratory support. Some other forms of organ support (e.g., renal replacement therapy) will be assessed as a secondary outcome measure. A full list of trial outcome measures can be found in **Table 3**. Due to the nature of the trial, it will not be possible to blind the outcome assessments.

**TABLE 3. T3:** Trial Outcome Measures

Primary outcome—clinical effectiveness
• Composite of mortality and duration of invasive mechanical ventilation from randomization to day 30
Primary outcome—cost-effectiveness:
• Incremental net monetary benefit, evaluated at the U.K. National Instiute for Clinical Excellence recommended threshold of £20,000 per quality-adjusted life year at 12 mo
Secondary outcomes
• Mortality at PICU discharge, 30 d, 90 d, and 12 mo
• Duration of survival to 12 mo
• Time to first liberation from invasive ventilation
• Functional status change between PICU admission and PICU discharge, measured by the Pediatric Overall Performance Category and Pediatric Cerebral Performance Category scales (30)
• Receipt of renal replacement therapy at 30 d
• Length of PICU and hospital stay
• Health-related quality of life at 1 yr, measured by the child self- or parent-proxy reported Pediatric Quality of Life Inventory 4.0 (31) with age-appropriate versions covering the wide range included in the trial (1 mo–16 yr) and the Child Health Utility 9D Index (32)
• Incremental costs at 30 d

